### Control group

Children assigned to the control group will receive a bolus injection of 1 μg/kg fentanyl intravenously before skin incision. During the operation, anesthesia will be maintained with 60% nitrous oxide, 40% oxygen, and 2% end-tidal sevoflurane. If the increases in the heart rate, noninvasive blood pressure, and respiratory rate are greater than 15% of the baseline values during the operation, then the concentration of sevoflurane will be increased by 0.5%. Conversely, if the heart rate, noninvasive blood pressure, and respiratory rate are reduced by greater than 15% of the baseline values during the operation, then the concentration of sevoflurane will be decreased by 0.5%. Furthermore, if the heart rate, blood pressure, and respiratory rate increase by greater than 25% of the baseline values during the surgery, then children will receive an additional bolus of 1 μg/kg fentanyl.

### Intraoperative anesthetic management and postoperative assessment

If the heart rate is reduced to less than 50 beats per min during the operation, then 10 μg/kg atropine will be used. If the blood pressure is reduced by greater than 25% of the baseline value, then 0.1 mg/kg ephedrine will be administered. At the end of surgery, sevoflurane will be discontinued, and the fresh gas flow will be increased to 6 l/min.

After completion of the operation, children will be transferred to the PACU and observed until the end of the study period. ECG results, noninvasive blood pressure, and pulse oximetry will also be measured every 5 min. After recovery of adequate of spontaneous breathing, purposeful movement, and eye opening, the endotracheal tube will be removed.

EA will be assessed using the PAED scale (Table 1) [24] at 0, 5, 10, 20, and 30 min after emergence from anesthesia. The PAED score will be documented by the same well-trained doctor, who will be blinded to the allocation group. The PAED score consists of five psychometric items: eye contact with the caregiver, purposeful action, awareness of surroundings, restlessness, and inconsolability. Each item is scored on a 5-point scale (0–4). The maximum score is 20. EA is defined as a PAED score greater than 10 points [25]. Patients with severe EA (PAED score ≥ 13) [24] will be treated with a bolus of 0.5 μg/kg fentanyl. The incidence of EA, frequency of severe EA, and duration of EA will be documented.

**Table 1 Tab1:** Pediatric Anesthesia Emergence Delirium (PAED) scale

1. The child makes eye contact with the caregiver	
2. The child’s actions are purposeful	
3. The child is aware of his/her surroundings	
4. The child is restless	
5. The child is inconsolable	

Items 1, 2, and 3 are reverse scored as follows: 4 = not at all, 3 = just a little, 2 = quite a bit, 1 = very much, 0 = extremely

Items 4 and 5 are scored as follows: 0 = not at all, 1 = just a little, 2 = quite a bit, 3 = very much, 4 = extremely

Scores for each item are summed to obtain a total PAED score between 0 and 20

Postoperative pain will be evaluated using the CHEOPS by a blinded observer at 0, 5, 10, 20, and 30 min after emergence from anesthesia in the PACU. The CHEOPS is a pain-scoring method applied for children aged 1–7 years. The scale was established by McGrath et al. [26]. The CHEOPS consists of six items: crying, facial expression, verbalization, torso position, touching of the affected area, and leg movement. The maximum score is 13, and the minimum score is 4 points. Children with CHEOPS score ≥ 4 will be treated with a bolus of 0.5 μg/kg fentanyl.

Hemodynamic changes and complications will be recorded in the PACU and compared between the two groups.

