### Data collection and management

Clinical characteristics include age, gender, weight, body mass index (BMI), ASA grade, duration of surgery, and duration of anesthesia (from induction of anesthesia to the discontinuation of sevoflurane).

Intraoperative data collection will include the following parameters: heart rate, noninvasive blood pressure, respiratory rate, dose of sevoflurane, and collective fentanyl dose.

Postoperative data collection will include the PAED score at every time point, incidence of EA, frequency of severe EA, duration of EA, time of emergence (from discontinuation of sevoflurane to the first response to a simple verbal command), extubation time (from the end of anesthesia to extubation), CHEOPS score at every time point, the incidence of complications and adverse events, and the dose of fentanyl in PACU.

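### The EA definition (PAED total above 10) can be met with no agitation at all: a calm child asleep again at a scheduled assessment scores 12 and counts as a case

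*Protocol article*

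**What the plan says.** All the relevant rules but one are in the protocol article under *Intraoperative anesthetic management and postoperative assessment*, including Table 1.

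- Case rule: "EA is defined as a PAED score greater than 10 points". Severe EA is a score of 13 or more.
- Scoring: "Items 1, 2, and 3 are reverse scored as follows: 4 = not at all, 3 = just a little", down to 0. For the agitation items, "Items 4 and 5 are scored as follows: 0 = not at all, 1 = just a little", up to 4. "Scores for each item are summed to obtain a total PAED score between 0 and 20".
- Timing: PAED is scored "at 0, 5, 10, 20, and 30 min after emergence from anesthesia".
- State of the child at the start: "After recovery of adequate of spontaneous breathing, purposeful movement, and eye opening, the endotracheal tube will be removed". *Data collection and management* defines "time of emergence (from discontinuation of sevoflurane to the first response to a simple verbal command".

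The primary outcome is the incidence of EA 30 min after emergence. That wording can mean EA at the 30-minute assessment or EA at any assessment up to 30 minutes. Duration of EA is a secondary outcome, and the article gives no rule for computing it. It requires no minimum on the restlessness or inconsolability item, and it has no rule for a child who is asleep when an assessment falls due.

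**The concern.** The outcome is called emergence agitation, but three of the five items measure lack of contact and awareness. A sleeping child gets the maximum on those three. If the total alone decides, quiet sleep is recorded as agitation.

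Sleep within the 30-minute window is plausible under this protocol. All children receive midazolam and fentanyl at induction, and fentanyl may be given in the PACU for severe EA or for pain. The article gives the CHEOPS minimum as 4 and also treats at a CHEOPS of 4 or more. As written every child would qualify, and those two statements must be reconciled.

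The primary comparison is at stake. False cases in both arms pull the difference towards zero, and false cases that are unequal between arms can bias it in either direction. Blinded assessment does not help, because the error lies in the scoring rule and not in the rater. Duration could also be affected: a child who settles to sleep after rescue moves from 13 or more down to 12, which is still above the cutoff.

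**Working it through.** **1. Scale range.** Five items scored 0 to 4 give 5 × 4 = 20, so the stated range of 0 to 20 reproduces.

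**2. Calm child, items 4 and 5 both 0.** The maximum is 3 × 4 = 12. Items 1 to 3 have 5 × 5 × 5 = 125 combinations. Those with a total above 10 are:

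- 4/4/4 = 12 (one pattern)
- 4/4/3 in any order = 11 (three patterns)

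This makes 4 of 125. It is a count of patterns, not a frequency in children. The nearest other patterns do not count as EA: 4+3+3 = 10 and 3+3+3 = 9. A calm child therefore becomes a case only when two of the three items are rated not at all and the third no better than just a little, which means asleep or nearly unresponsive. None of the 125 patterns reaches 13.

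**3. When it can happen.** Time is counted from emergence. The end of emergence time is the first response to a command, and extubation needs purposeful movement and eye opening. The child has therefore been responsive by about time 0, and the gap concerns children who fall asleep again, mainly at the later assessments.

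**4. What it could do to incidence.** Let p be the true EA rate and s the share of non-EA children scored 11 or 12 while calm. The observed rate is p + s(1 − p). With the same s in both arms, the true difference is multiplied by (1 − s). The control rate of 42% is from *Sample size estimation*. The 27% reads the stated 15% reduction as absolute, which is an assumption. Every value of s is an assumption, because the documents give none.

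| s control | s block | Control | Block | Difference (points) |
|---|---|---|---|---|
| 0 | 0 | 42.0% | 27.0% | 15.0 |
| 10% | 10% | 0.42 + 0.1 × 0.58 = 47.8% | 0.27 + 0.1 × 0.73 = 34.3% | 13.5 |
| 20% | 20% | 0.42 + 0.2 × 0.58 = 53.6% | 0.27 + 0.2 × 0.73 = 41.6% | 12.0 |
| 10% | 20% | 47.8% | 41.6% | 6.2 |
| 20% | 10% | 53.6% | 34.3% | 19.3 |

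At 45 per group and two-sided 5%, power is 32% in the first row and 20% in the third. The first figure already differs from the stated 80%, which is a separate matter. With no true effect and 42% in both arms, s of 20% in control and 10% with block would give a false difference of 0.58 × (0.20 − 0.10) = 5.8 points.

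**5. Duration.** If duration is taken from consecutive scores above 10, sleep after rescue extends it, since 12 exceeds 10. The article does not say that it is taken this way.

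**The case against.** Five objections deserve an answer.

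*The article is condensed.* How to score a sleeping child may be in a full protocol or in rater training, and the article names one well-trained, blinded assessor. This has weight. But the article prints the complete case rule, with items, cutoff and times, and a rater who follows it as printed will misclassify a sleeping child. That goes beyond missing detail.

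*The child is awake by definition.* A reader might infer that PAED is scored whether or not the child is awake. The text does not say so, and it starts the clock with a responsive child. What stands is that one response to a command does not keep a child awake for 30 minutes.

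*Drowsiness is not enough.* A reader might take any drowsy child to score 12. That is wrong, because 3 on each of items 1 to 3 totals 9. Nor can calm sleep raise the frequency of severe EA.

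*Direction.* It is tempting to argue that control children are more sedated, since they receive an extra 1 μg/kg of fentanyl before incision. Nothing in the documents shows that this still sedates them during the PACU assessments, so no direction follows. The unequal rows in the table show only that bias is possible. Also, sleep after rescue for severe EA cannot create a new case under the any-time reading, because that child has already exceeded 10.

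*The cutoff is cited.* PAED is a summed scale, and classing every awake child with items 4 and 5 at 0 as free of EA would override it. This stands, and such a rule belongs in a sensitivity analysis.

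**Conclusion.** The point holds in a limited form. As printed, the definition of the primary outcome counts a calm child who is asleep, or nearly unresponsive, at a scheduled assessment as an EA case with a total of 11 or 12. This rests on Table 1 and addition alone. It affects incidence under either reading of the primary outcome, and it affects duration if duration is built from consecutive scores above 10. It does not extend to drowsy children in general or to severe EA, and it is of little concern at time 0.

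How often it happens, and whether it differs by arm, cannot be obtained from the documents. The shrinkage from 15 to 12 points rests on an assumed 20% in both arms and an assumed 42% vs 27%. It shows scale and does not estimate the bias.

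**What to change.** At each PAED time point, record whether the child is asleep or awake. Class a child who is asleep at that time as not having EA then, for both incidence and duration, and keep the cutoff of above 10 for awake children. EA recorded while awake at another time point still counts towards any-time incidence.

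Report two sensitivity analyses: the unmodified rule (any total above 10) and, if item scores are kept, a version that also requires item 4 or item 5 to be above 0. *Data collection and management* lists the PAED score at each time point but does not say that item scores are retained, so this should be confirmed.

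The article disagrees with itself on whether the trial is over: *Study time* says it was completed in October 2018, and *Trial status* says it is recruiting. If data collection has ended and sleep status was not recorded, run the item-based version before unblinding and state the limitation in the report.

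The cost is one tick-box per assessment, one sentence in the endpoint definition, and a small departure from the cited cutoff. The unmodified analysis keeps results comparable with other uses of that cutoff. If a fuller protocol already has a rule for sleeping children, stating it in the endpoint definition is enough.

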#### Secondary objectives

The secondary objectives are as follows:to compare the severity and duration of EA between the ultrasound-guided lumbar block group and the control group;to compare postoperative pain between the two groups; andto compare the occurrence of postoperative complications between the two groups.

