#### Secondary outcomes

The secondary outcomes are as follows:The severity and duration of EA 30 min after emergence from anesthesia evaluated using the PAED scale.The intensity of postoperative pain evaluated using the Children’s Hospital of Eastern Ontario Pain Scale (CHEOPS) scale.The incidence of postoperative adverse events.

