### Statistical analysis

Patient demographics will be compared between the two groups to ensure that the data are balanced.

Intention-to-treat analysis will be used to analyze data including failed block. A per-protocol set will then be used to analyze data excluding the data for failed block. Continuous variables with a normal distribution will be reported as the means with the SD, which will be analyzed by an independent-samples *t* test. Data for the PAED and CHEOPS will be analyzed by either one-way repeated-measures ANOVA or Friedman’s repeated ANOVA on ranks according to the test for normality and homogeneity of variance. Categorical variables, such as the incidence of EA, will be reported as numbers and percentages, and analyzed by the chi-square test or Fisher’s exact test as appropriate. The reduction in pain, the decreased sevoflurane dose, and the dose of fentanyl in the PACU, regarded as covariates for the incidence of EA, will be assessed using logistic regression.

Statistical tests will be conducted using SPSS 12.0 (SPSS Inc., Chicago, IL, USA), and *P* < 0.05 will be considered statistically significant.

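### Fentanyl given at PAED ≥ 13 falls inside the scoring window, yet no rule covers EA duration and later PAED scores after rescue, so these comparisons are likely to shrink toward no effect

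*Protocol article*

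**What the plan says.** Everything here is in the Methods of the Protocol article.

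- **Objective and outcome.** The first secondary objective is "to compare the severity and duration of EA between the ultrasound-guided lumbar block group and the control group". The matching entry under Secondary outcomes is "The severity and duration of EA 30 min after emergence from anesthesia evaluated using the PAED scale".
- **Scoring.** Under Intraoperative anesthetic management and postoperative assessment, PAED is scored "at 0, 5, 10, 20, and 30 min after emergence from anesthesia. The PAED score will be documented by the same well-trained doctor". EA is a score above 10.
- **Rescue.** The same section states: "Patients with severe EA (PAED score ≥ 13) [24] will be treated with a bolus of 0.5 μg/kg fentanyl". It then adds: "The incidence of EA, frequency of severe EA, and duration of EA will be documented".
- **Data.** Under Data collection and management: "Postoperative data collection will include the PAED score at every time point, incidence of EA, frequency of severe EA, duration of EA". PACU fentanyl is listed there as a dose, with no time and no trigger.
- **Analysis.** Under Statistical analysis: "Data for the PAED and CHEOPS will be analyzed by either one-way repeated-measures ANOVA or Friedman’s repeated ANOVA on ranks". PACU fentanyl enters only a logistic regression for the incidence of EA. The per-protocol set removes failed blocks, not rescued children.
- **Second fentanyl rule.** CHEOPS is scored at the same five times. A score of 4 or more also leads to a 0.5 μg/kg fentanyl bolus, on a scale whose stated minimum is 4.

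**The concern.** The outcome score triggers a treatment that can change the later course of the same outcome, and it does so only in the more severe cases. A child who peaks at 11 or 12 has EA but no PAED-triggered bolus. A child who reaches 13 is treated, and a shorter episode after that partly reflects fentanyl.

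If the block makes EA milder, more control children reach 13 and are rescued. Their recorded episodes are shortened and their later scores lowered more often than in the block group. The bias then works against an effective block, and a small or absent difference in duration could be misread as no benefit beyond incidence. The end of scoring at 30 min is a separate matter, because this mechanism acts within the window.

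**Working it through.** The plan gives no figure for EA duration by arm, the severe share of EA or the effect of rescue, so there is nothing of its own to reproduce. The checks below are illustrations.

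**Inputs from the article.** Control incidence of EA is 42%. The expected reduction is 15%, not stated as absolute or relative: 42 − 15 = 27%, or 0.42 × 0.85 = 35.7%. EA lasts 30 min on average (Background, not described as untreated).

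**Assumptions.** Untreated duration T is exponential with mean 30 min, the same in both arms, and counted to 30 min. EA is present at 0 min. Severe cases are rescued at 0 min, and rescue ends EA by 5 min. The severe share of EA cases is 50% in control and 25% with the block.

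**Step 1. Among children with EA.**
- Not rescued: E[min(T,30)] = 30(1 − e^−1) = 18.96 min
- Rescued: E[min(T,5)] = 30(1 − e^−1/6) = 4.61 min
- Control: 0.50 × 4.61 + 0.50 × 18.96 = 11.8 min
- Block: 0.25 × 4.61 + 0.75 × 18.96 = 15.4 min

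The true difference is zero, and the block appears 3.6 min worse. In general the distortion is the gap in severe share × (18.96 − 4.61 = 14.4 min), or 1.4 min for a 10-point gap. If rescue ends EA only by 10 or 20 min, the 25-point gap gives 2.6 or 1.1 min.

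**Step 2. Averaged over whole arms, children without EA counted as 0.**
- Block 27%, no rescue: 0.42 × 18.96 − 0.27 × 18.96 = 2.8 min in favour of the block. With rescue: 0.42 × 11.78 − 0.27 × 15.37 = 4.95 − 4.15 = 0.8 min.
- Block 35.7%, no rescue: 0.42 × 18.96 − 0.357 × 18.96 = 1.2 min. With rescue: 4.95 − 5.49 = −0.5 min.

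Under these inputs the sign changes once block incidence exceeds 0.42 × 11.78 / 15.37 = 32.2%.

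**Step 3. Different assumptions.** A simulation of 400,000 children per arm let severe EA last longer. Untreated duration was exponential with mean 25 min if severe and 15 min otherwise, capped at 30 min. Rescue shortened severe episodes by a set fraction. Whole-arm differences (control minus block, min):

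| Block incidence | Severe share, control / block | Shortening by rescue | Without rescue | Recorded |
|---|---|---|---|---|
| 27% | 60% / 60% | 50% | 2.3 | 1.8 |
| 27% | 60% / 60% | 90% | 2.4 | 1.0 |
| 27% | 60% / 30% | 50% | 2.7 | 1.7 |
| 27% | 60% / 30% | 90% | 2.7 | 0.2 |
| 27% | 80% / 20% | 90% | 3.2 | −1.0 |
| 35.7% | 60% / 30% | 50% | 1.4 | 0.6 |
| 35.7% | 60% / 30% | 90% | 1.5 | −0.7 |

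The difference shrank in every scenario with a rescue effect above zero. Among EA cases only, reversal comes sooner: at shares 60% / 30% and 50% shortening, 15.7 v 14.3 min becomes 12.0 v 12.4 min.

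**Step 4. Which measures are exposed.** Whether a child ever reaches 13 is settled before the bolus which that score triggers. Duration and all scores after the bolus are exposed.

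**The case against.** **The premise may fail under the CHEOPS rule.** A trigger of 4 or more on a scale that starts at 4 covers every possible score. Read literally, all children in both arms receive PACU fentanyl, those at PAED 11–12 included, and the rescue contrast between arms is lost. This stands as a limit on the size of the effect. It rests on a passage that contradicts itself, so it does not make the duration outcome sound.

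**Severity remains answerable.** A reader might infer that the whole first secondary objective is lost. The article does not support that, because the frequency of severe EA is recorded and is not distorted by the PAED-triggered bolus.

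**Reversal is not the expected result.** A reader might take 11.8 v 15.4 min as the likely finding. It covers EA cases only, on inputs that the article does not give, and the article does not say over which children duration is averaged. At 27% the whole-arm result keeps its sign.

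**Some of this is inferred.** The article does not say that the bolus is immediate or that later scores enter the analysis as observed. Comparing outcomes under care that includes rescue is also a legitimate treatment-policy question, and an analysis plan not shown may address it. However, the article does fix the PAED analysis and the sole use of PACU fentanyl, and it lists only the dose. With two triggers for the same bolus, dose alone cannot show which bolus was for EA or when it was given.

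**A composite has its own tilt.** With identical untreated durations, counting rescued children as 30 min gives 0.50 × 30 + 0.50 × 18.96 = 24.5 min in control and 0.25 × 30 + 0.75 × 18.96 = 21.7 min with the block. Read as pure duration, that is a false 2.8-min advantage for the block. This stands, and it governs how the composite must be labelled.

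**Conclusion.** The concern holds for EA duration and for PAED scores after rescue. If severe EA is commoner in control, the plan as written is expected to pull these comparisons toward no effect. In the illustrations at 27% block incidence, the whole-arm advantage falls from 2.8 to 0.8 min, or from 2.7 to 1.7 min under milder assumptions. These sizes rest on assumed severe shares, rescue effects and duration distributions.

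Reversal is possible only under stronger conditions: averaging over EA cases only, a block incidence near 35.7%, or severe EA heavily concentrated in control with a large rescue effect. The frequency of severe EA, counted as children who ever reach 13, is not distorted by the bolus it triggers. If the CHEOPS rule is applied literally, the contrast in rescue on which the bias depends disappears.

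**What to change.** Leave the rescue rule as it is and change the outcome rules.

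1. **Severity.** Compare the frequency of severe EA and the peak PAED up to and including the first score ≥ 13, rather than relying on post-rescue scores. This peak will not show a child who worsens after rescue.
2. **Duration.** Analyse time to EA resolution without rescue, counting a child who reached PAED ≥ 13 and was rescued as not resolved through 30 min. Label it as a composite. Report observed duration, rescue included, beside it as a treatment-policy result.
3. **Data.** Record the time and triggering score (PAED or CHEOPS) of each PACU fentanyl bolus, and report rescue by arm.
4. **Reconcile.** The CHEOPS fentanyl trigger and the stated CHEOPS minimum must be reconciled with each other. Which of them should change is not for this review.

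The cost is outcome wording and two recorded fields per bolus. The downside is that the composite mixes duration with need for rescue and favours the arm with fewer severe cases, so it should not be read alone. If bolus times and triggers were not captured for children already treated, item 2 can be applied to them only as far as source records allow.

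### The CHEOPS trigger for rescue fentanyl (≥ 4) equals the scale's stated minimum of 4, so the rule as written excludes no child, and the text does not show which number is wrong

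*Protocol article*

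**What the plan says.** The rule is in the protocol article, under Intraoperative anesthetic management and postoperative assessment.

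- **Timing of pain scores:** "Postoperative pain will be evaluated using the CHEOPS by a blinded observer at 0, 5, 10, 20, and 30 min after emergence".
- **Range of the scale:** "The maximum score is 13, and the minimum score is 4 points".
- **Pain rescue, in the next sentence:** "Children with CHEOPS score ≥ 4 will be treated with a bolus" of 0.5 μg/kg fentanyl.
- **Agitation rescue, same section:** "Patients with severe EA (PAED score ≥ 13) [24] will be treated with a bolus" of the same drug at the same dose. PAED is scored at the same five times as CHEOPS, and "EA is defined as a PAED score greater than 10 points".

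Pain is also an outcome. One of the Secondary objectives is "to compare postoperative pain between the two groups", and Secondary outcomes lists pain intensity on CHEOPS. Data collection and management records the PACU fentanyl dose. Statistical analysis names that dose as a covariate for the incidence of EA.

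**The concern.** A rescue threshold is meant to separate children who need analgesia from those who do not. A threshold equal to the lowest attainable score cannot do this, and here it governs an opioid for children aged 1 to 6.

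Two things are at stake:

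- **If staff follow the text,** a child with the lowest possible pain score qualifies for fentanyl on emergence. Every later PAED and CHEOPS score is then taken after rescue was due. That touches EA incidence, severity and duration, and the pain comparison. The Background section itself holds that good pain control can lower EA, so an analgesic rule applied within the assessment window is relevant to the trial's question.
- **If staff use some other, unwritten cut-off,** a reader cannot tell what rule produced the PACU fentanyl doses or the scores that followed them.

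**Working it through.** **Inputs** (all from Intraoperative anesthetic management and postoperative assessment): CHEOPS minimum 4 and maximum 13; CHEOPS trigger ≥ 4; bolus 0.5 μg/kg; assessments at 0, 5, 10, 20 and 30 min; PAED trigger ≥ 13. The protocol derives no figure here, so there is none to reproduce.

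**Step 1: scores that meet the trigger.**
- Whole-number scores in the stated range: 13 − 4 + 1 = 10.
- Scores of 4 or more: 10.
- Scores excluded: 10 − 10 = 0.

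**Step 2: what each explanation would imply.**
- *The trigger is wrong.* A cut-off c above 4 is met by 13 − c + 1 scores: 9 of 10 for ≥ 5, 8 for ≥ 6, 7 for ≥ 7 and 6 for ≥ 8. These count score values, not children, and are illustrations only. Nothing in the document selects among them.
- *The stated minimum is wrong.* With a true minimum m below 4, the trigger would exclude 4 − m scores. The section lists six CHEOPS items but no item scores, so m cannot be rebuilt from the text.
- *Rescue is unconditional.* The rule then works as written, but its conditional wording serves no purpose.

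**Step 3: literal consequence.** Every child assessed qualifies at 0 min, in both arms. Four of the five assessments (5, 10, 20 and 30 min) come after that point; scores at 0 min need not be affected. The text does not say whether the bolus repeats. On the assumption of one to five boluses, the total would run from 0.5 to 5 × 0.5 = 2.5 μg/kg.

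**Step 4: the agitation trigger.** If every child already qualifies through CHEOPS, PAED ≥ 13 no longer decides who receives any fentanyl rather than none. Children with EA below the severe threshold (PAED 11 or 12) have no fentanyl order under the agitation rule but would have one under the pain rule. PAED ≥ 13 could still order an additional bolus, because the text does not make the two orders exclusive.

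**Step 5: search for another cut-off.** No other CHEOPS threshold appears in the text. The two figures are not shown and could not be checked.

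**The case against.** The strongest reply is that this is a misprint that never reached the bedside: staff used a sensible cut-off, and universal rescue did not happen. That may well be so. The sentence is worded as a condition, and a separate, selective agitation trigger for the same drug and dose would be largely idle if everyone were already treated. But the document does not confirm it, and a misprinted opioid threshold still has to be corrected.

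Several stronger readings are tempting and not supported:

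- *The trigger is certainly the wrong number.* The stated minimum could be the error instead.
- *Using PACU fentanyl as a covariate proves that rescue was meant to be selective.* The covariate is dose, not receipt. Dose could vary through repeat boluses or an added agitation bolus even if every child qualified.
- *The EA comparison is biased.* The rule is identical in both arms. Blinding extends to PACU staff and assessors. A common rescue rule might lower EA in both arms and narrow the difference, but nothing in the document fixes the size or the direction of any effect.

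Nor is this a detail that a condensed article may leave to the full protocol. The article states the range, the threshold, the drug and the dose, and the range and threshold together leave the rule without effect.

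**Conclusion.** Wrong as written. The CHEOPS trigger equals the stated scale floor, all 10 of 10 scores qualify, and the text does not allow the intended rule to be recovered. This is certain from two adjacent sentences and needs no outside source.

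The consequences are conditional. Universal opioid rescue, and outcome scores measured under it, follow only if the rule was applied literally. No bias in the primary comparison is shown. The weight of the point rests on a dosing instruction that cannot discriminate between children. The count of 10 assumes whole-number scores and the range as printed.

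**What to change.** The investigators should reconcile the two numbers: either replace the trigger with a clinically chosen cut-off above the scale minimum, or correct the stated minimum if that is the error. The value is theirs to set; the document offers none.

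The article's Study time section says the study was completed in October 2018, while Trial status says it is still recruiting. If it is complete, the report should state the cut-off actually applied. If that was ≥ 4 on a 4 to 13 scale, it should give PACU fentanyl by arm and describe the EA and pain results as obtained under universal opioid rescue.

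The cost is one corrected sentence and, in the last case, one by-arm summary of a variable already being collected.
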